## Methods/Design

This protocol proposes a randomised controlled trial to determine the efficacy of the MHFA training for university nursing students (see Figure 1). Participants will be randomly allocated to the intervention group (receiving MHFA training during the study) or the control group (not receiving MHFA training during the study and waitlisted to receive an online version of the course on completion of the intervention). Participants receiving the intervention will attend a MHFA course comprising two-6.5 hour face-to-face sessions run over two days. The study follows the CONSORT Guidelines [64] for the design and implementation of randomised controlled trials.

**Figure 1 Fig1:**
[figure not shown]
**Trial schema.**

### Participants and sample size

The source population will be undergraduate nursing students at a large university located in Perth, Western Australia. Criteria for inclusion: 1) first year undergraduate nursing student; 2) enrolled in the internal study mode; 3) studying at the Curtin University Bentley campus; and 4) aged 18 years or older. The size of the sample has been determined by the practicalities of working in a large university which requires delivering the intervention during semester at a time convenient to university scheduling requirements and clinical rotations for the students. Assuming a high correlation of 0.8 for the baseline-post measurements [65,66], it will be necessary to have 50 students in each group to detect 5% level of significance with 90% power in order to detect medium effect sizes in the outcome variables [57]. A total of 63 students will be recruited for each group to account for 20% attrition from baseline to post intervention.

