### Statistical analyses

The intention-to-treat principle will be followed, where all participants who completed the baseline questionnaire will be included in the analysis regardless whether they complete the whole intervention. Acknowledging there may be attrition at the follow-up, the missing values for the non-respondents will be recorded using their baseline scores. If the missing data are at random, the imputation method will be applied [59]. This will assure no false improvement in efficacy. Data will be analysed using SPSS Version 22.

The demographics of the participants in the intervention and control groups will be compared using the independent samples t-test or Pearson’s Chi-square test to measure differences including age, gender and country of birth. The primary outcome measures (described above) will be calculated following validated MHFA scoring methods reported in the literature [44,54,57,65-68]. Repeated measures analysis of variance will be employed to assess continuous measures between the intervention and control group over three time points (baseline, post intervention and two months post intervention). Logistic regression will be used to assess changes in dichotomous variables. The significance level will be set at 5%.

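### The single 90% power claim at 50 per group is not reproduced if a medium effect means 0.5 SD, and is not supported for dichotomous outcome measures

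*Protocol article*

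**What the plan says.** Under *Participants and sample size*, the protocol article first says that the size was set by what university scheduling allows. It then gives a power statement. The correlation input is "Assuming a high correlation of 0.8 for the baseline-post measurements". The result is "it will be necessary to have 50 students in each group to detect 5% level of significance with 90% power", and its scope is "in order to detect medium effect sizes in the outcome variables", with a citation for the effect size but no number. Recruitment is then inflated: "A total of 63 students will be recruited for each group" "to account for 20% attrition from baseline to post intervention".

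Under *Statistical analyses*, two methods are named. For scales: "Repeated measures analysis of variance will be employed to assess continuous measures between the intervention and control group over three time points". For the rest: "Logistic regression will be used to assess changes in dichotomous variables". The test level is 5%, with sidedness not stated. The article does not list which measures are dichotomous. The sentence on logistic regression follows directly on the scoring of the primary outcome measures, so it is a fair inference, though not a stated fact, that some of these are dichotomous.

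**The concern.** One power figure is attached to all outcome variables, but it rests on an input (a 0.8 correlation between baseline and follow-up) that helps only where the analysis uses baseline and the measure carries that correlation. Two questions follow. Does 50 per group come out of the printed inputs for the continuous scales? And can the same 90% be claimed for measures analysed by logistic regression?

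The second matters more for interpretation. A null result on a dichotomous measure could be read as coming from a comparison with 90% power when its power was well below that.

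**Working it through.** **Inputs from the article:** 5% level; 90% power; correlation r = 0.8; equal groups; 50 per group analysed; 20% attrition.

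**Assumptions:** two-sided test; medium = 0.5 SD for continuous scales and Cohen's h = 0.5 for proportions.

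**Step 1, attrition.** 50 / (1 − 0.20) = 62.5, rounded up to 63. The plan's recruitment figure is reproduced.

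**Step 2, continuous scales.** With variance factor k, the normal approximation is n per group = 2 × (1.960 + 1.282)² × k / d². At d = 0.5 this is 84.1 × k. The effect detectable with 90% power at n = 50 is (1.960 + 1.282) × √(2k/50) = 0.648 × √k. The noncentral t version adds one person per group.

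| Contrast | k at r = 0.8 | n, normal | n, noncentral t | Power at 50 (noncentral t) | Effect for 90% at 50 (normal) |
|---|---|---|---|---|---|
| Baseline-adjusted | 1 − r² = 0.36 | 31 | 32 | 98.5% | 0.39 SD |
| Change score | 2(1 − r) = 0.40 | 34 | 35 | 97.5% | 0.41 SD |
| Group main effect, mean of three times | (1 + 2r)/3 = 0.867 | 73 | 74 | 75.8% | 0.60 SD |
| Group main effect, mean of two times | (1 + r)/2 = 0.90 | 76 | 77 | 74.2% | 0.62 SD |
| Follow-up only | 1 | 85 | 86 | 69.7% | 0.65 SD |

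No row gives 50 at d = 0.5. One-sided tests at 90% give 25 (baseline-adjusted), 28 (change score) and 69 (follow-up only). A group-by-time interaction at f = 0.25, which defines the effect differently, gives 8 to 10 per group. At d = 0.5, 50 was reached only by leaving the stated inputs: a one-sided follow-up comparison at 80% power, or a change score tested at 0.05/6.

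The main-effect rows treat 0.5 SD as the difference averaged over the time points. Randomised groups should start level, so averaging in the baseline would shrink that difference; these rows are not pessimistic.

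Keeping the stated 5%, 90% and 0.8, a baseline-using contrast gives 50 when the effect is about 0.39 SD (baseline-adjusted) or 0.41 SD (change score). Larger effects also give 50 for the lower rows. The follow-up-only row does so at 0.65 SD, but there the 0.8 correlation plays no part.

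**Step 3, dichotomous measures.** With no gain from baseline, the arcsine approximation is power = Φ(h × √(n/2) − 1.960). At n = 50, √(n/2) = 5.

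- h = 0.5: Φ(2.50 − 1.96) = Φ(0.54) = 71%. Example: 50% versus 74%.
- h = 0.39: Φ(1.95 − 1.96) = Φ(−0.01) = 50%.
- h = 0.41: Φ(2.05 − 1.96) = Φ(0.09) = 54%.
- 90% power: h = (1.960 + 1.282)/5 = 0.65, roughly 50% versus 80%.
- n for 90% at h = 0.5: 2 × (1.960 + 1.282)² / 0.25 = 84.1, so 85 per group.

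The pooled two-proportion formula at h = 0.5 gives 66–70% for control rates from 10% to 80%. For other illustrative pairs at 50 per group it gives 53% (50% versus 70%), 74% (50% versus 75%) and 89% (50% versus 80%).

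**The case against.** The strongest reply is that *medium* is tied to a cited study, and 0.5 SD is only the conventional value. An effect of about 0.39–0.41 SD reproduces 50 with a baseline-using contrast. This stands. A reader might infer that the protocol contains an arithmetic error; the article does not support that, because it does not print the effect size. Nor is the missing number a fault in itself, since an article may leave the numerical effect, formula and sidedness to a fuller document.

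It is also right that for continuous scales the mismatch at 0.5 SD is in the safe direction, provided the tested term uses baseline. A reader might infer that the trial is too small for its scales. That would hold only if the group main effect were the test, and the article does not say that it is.

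A reader might also take 71% as the trial's power for its dichotomous measures. The article gives no event rates, does not name those measures, and does not say whether the logistic model conditions on baseline. It also does not say that 0.8 belongs only to continuous scores. The figure is therefore conditional. The reply does not rescue the 90%, however: the smaller effect that explains 50 lowers dichotomous power to about 50–54%, and nothing in the article shows a baseline gain large enough to close the gap.

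The intention-to-treat rule keeps all baseline completers, so 63 per group may enter the analysis. Even counting all 63 as fully informative, h = 0.5 gives Φ(0.5 × √31.5 − 1.96) = 80%, and carrying baseline scores forward adds no follow-up information.

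Finally, a reader might infer that the 20% allowance leaves the two-month comparison unprotected. Both follow-ups are titled post-intervention questionnaires, so the allowance may cover both, and no further loss is stated from which a shortfall could be computed.

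**Conclusion.** The point holds in two parts.

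First, if medium means 0.5 SD, the stated 50 is not reproduced, and the true power depends on a term that the article does not name: about 97–98% for a baseline-using contrast, about 74–76% for a group main effect. The printed 90% matches neither. It does match a baseline-using contrast with an effect of about 0.39–0.41 SD.

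Second, and independently of how the first is resolved, 90% is not supported for measures analysed by logistic regression. With 50 per group, a two-sided 5% test and no baseline gain, power is about 71% at h = 0.5 (66–71% by formula and control rate) and about 50–54% at h = 0.39–0.41. It reaches 90% only near h = 0.65.

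This rests on treating h as the counterpart of the standardised difference and on illustrative rates. It is a fault in the scope of a stated power, not a reason to change the design.

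**What to change.** Keep 63 per group and restate what 50 analysed per group provides:

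- Limit the 90% statement to the continuous scales. Print the numerical effect and the contrast it refers to (baseline-using or group-by-time). At a correlation of 0.8 this is about 0.39 SD baseline-adjusted or 0.41 SD for change from baseline to one follow-up. If the overall group-by-time test across three time points is the one intended, compute the figure for that test.
- Add a separate, explicitly conditional figure for dichotomous measures.

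Possible wording:

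> With 50 per group analysed, a two-sided 5% test and a baseline-post correlation of 0.8, the trial has 90% power to detect about 0.39 SD (baseline-adjusted) or 0.41 SD (change score) on continuous scales. No event rates were assumed for dichotomous measures; as an illustration, 50 per group gives about 71% power for 50% versus 74%, without adjustment for baseline.

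The cost is wording only. There is no extra recruitment, but the stated power for dichotomous measures becomes less favourable.

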### Ethical approval

In order to eliminate any harm associated with not receiving the MHFA training, the control group will be offered an online version of the intervention at the end of this study after all participants have completed the two-month post intervention questionnaire. The online course covers the same content as the face to face course and takes around six to eight hours to complete. This study has been granted ethical approval by the Curtin University Human Research Ethics Committee, approval number: SPH-74-2013.

#### Stage 1: recruitment and group allocation

First year undergraduate nursing students will be contacted through email, fliers, and in-class announcements. Potential participants will be provided an information sheet and asked to provide consent if they agree to participate via the online survey. Students who agree to participate will complete a pre-intervention questionnaire and be randomly assigned to the intervention or control group through automated randomisation. Each participant will be provided with a de-identifiable code to ensure anonymity.

#### Stage 2: baseline questionnaire

Participants from the intervention and control groups will be asked to complete an online baseline questionnaire (occurring at the same time), which will be one week prior to the intervention. Participants will be emailed a link to the online survey. A reminder email will be sent once after the initial contact.

#### Stage 3: the intervention

The intervention group will receive Mental Health First Aid training. The MHFA training will consist of two 6.5 hour sessions, delivered face to face, which include:Signs, symptoms and risk factors of common mental health problems including depression, anxiety and substance use disorders, eating disorders and psychosis;Strategies to assist an individual who may be experiencing a mental health crisis such as a panic attack or suicidal thoughts or suicidal behavior; andWhat works to help those developing or experiencing a mental health problem or crisis [41].

Participants will be provided with standardised Mental Health First Aid materials, including the Mental Health First Aid Manual and additional tailored materials designed for nurses. Four courses of up to 20 students per course will be delivered over a period of two weeks by a team of three qualified MHFA facilitators who will include a mental health nurse and a community health promotion practitioner and a university academic. The third facilitator will provide consistency across all courses. The standardised MHFA training for nursing students will be piloted by the teaching team prior to the commencement of the intervention to ensure that the approach and delivery of the materials is consistent. Further information about the program has been described by the MHFA research team [54].

#### Stage 4: post-intervention questionnaire one

Immediately after course completion, the intervention group will be asked to complete the post intervention questionnaire in the classroom via i-pad. The control group will be emailed the same questionnaire at the same time. An email reminder will be sent twice a week for two weeks to those who do not respond in the first instance.

#### Stage 5: post-intervention questionnaire two

Two months after the MHFA course is delivered, the second post-intervention questionnaire will be emailed to all participants. An email reminder will be sent twice a week for two weeks to those who do not respond in the first instance.

#### Stage 6: MHFA for the control group

The waitlisted control group will be provided with access to the online version of the Mental Health First Aid training and will receive a copy of the MHFA training manual after the second post-intervention questionnaire is administered. Additionally, participants from the intervention group who complete the baseline questionnaire but do not complete the MHFA training will be provided an opportunity to undertake the online course at the completion of the intervention along with the control group.

#### Stage 7: process evaluation

Participant satisfaction with training content, materials, facilitators, venue and timing will be determined using a standard MHFA training evaluation form. Program reach and engagement will also be assessed by the initial participation rate and response rate at the end of the study.

#### Stage 8: follow up

A follow up will be conducted at 12 months. Participants from the intervention group will be invited to take part in a short follow up questionnaire to determine to what extent participants have maintained knowledge, skills and confidence and explore any opportunities they have had to use their skills and the impact that the training has had on this experience.

### Instruments

A self-report questionnaire will measure confidence to respond to mental health problems, recognition of and knowledge about mental health problems, first aid intentions towards someone experiencing a mental health problem, stigmatising attitudes [67] and social distance [68-70]. The questionnaire is based on those used in national surveys of adults [43] and young people [71] and further developed for use with the MHFA course [54,65,69], and described in detail in previous studies [44,57,72]. Questions related to confidence, recognition, intentions, stigmatising attitudes and social distance will be introduced with a vignette describing a young person with symptoms of a mental health problem. The use of the vignette to introduce mental health issues has been used successfully by other studies, including those of MHFA [44,57,68,72]. Participants will be asked about their level of confidence to help and what they would do to assist the person in the vignette [65]. Knowledge will be measured using 16 questions developed by MHFA and modified for use with young people [66]. Stigmatising attitudes will be measured using personal and perceived stigma scales [67], and social distance will be measured using a five item social distance scale [68]. The scales have been used widely and previously tested for reliability and validity; the stigma scales have demonstrated test-retest reliability and acceptable internal consistency while the social distance scale has been shown to be a reliable measure of stigma towards people with mental health problems and to be valid as a proxy measure for rejection of and discrimination toward people with mental health problems and disorders [67,69,70,73]. The questionnaire will be administered to the intervention and control group participants at three time intervals: baseline, immediately post, and two months after the intervention. Basic socio-demographic characteristics of participants will be collected at baseline only.

In addition, the questionnaire administered immediately post training will collect process evaluation data to measure participant satisfaction with the relevance and calibre of the MHFA training. A follow up questionnaire will be administered at 12 months post study with participants from the intervention group to explore participant experiences with using knowledge and skills from the training, interactions with individuals they thought may have a mental health problem; and for those who had not had an opportunity to use their training directly, gauge expectations, intentions and confidence to provide help.

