The Australian Government Department of Health has provided funding to Mental Health First Aid Australia [62] to specifically train frontline staff including financial counsellors and healthcare professionals (including pre-service nursing students) to better identify and respond to the needs of people at risk of mental health problems and disorders. The aim of the course developed for nursing students is to teach them how to assist a peer who is developing a mental health problem or in a mental health crisis. The course is available both as a face to face version and as an e-course online [63].

This paper presents a protocol for a pragmatic, low-cost trial to examine the efficacy of the MHFA training for students studying nursing at a large university in Perth, Western Australia. The primary outcome is changes in mental health literacy, which will be measured in terms of confidence in dealing with mental health problems, recognition of and knowledge about mental health problems, first aid intentions, stigmatising attitudes and social distance.

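### The two-month knowledge test is emailed when only the trained arm has been given the MHFA manual, so the knowledge difference may partly reflect look-up

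*Protocol article*

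**What the plan says.** All references are to the protocol article.

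- **Outcome.** The section Mental health first aid states: "The primary outcome is changes in mental health literacy". It lists knowledge about mental health problems among the components.
- **Measure.** Under Instruments: "Knowledge will be measured using 16 questions developed by MHFA and modified for use with young people". The same section sets the waves: "The questionnaire will be administered to the intervention and control group participants at three time intervals: baseline, immediately post, and two months after the intervention".
- **Manual, trained arm.** Stage 3: "Participants will be provided with standardised Mental Health First Aid materials, including the Mental Health First Aid Manual".
- **Manual, control arm.** Stage 6 says that controls "will receive a copy of the MHFA training manual after the second post-intervention questionnaire is administered". Ethical approval likewise holds the online course back until the two-month questionnaire is done.
- **Mode at two months.** Stage 5: "the second post-intervention questionnaire will be emailed to all participants", followed by: "An email reminder will be sent twice a week for two weeks to those who do not respond in the first instance". No supervised sitting is described.
- **Mode immediately after the course.** Stage 4: "the intervention group will be asked to complete the post intervention questionnaire in the classroom via i-pad". Controls get the same questionnaire by email.
- **Analysis.** Under Statistical analyses, continuous measures go into a repeated measures ANOVA over the three time points, and non-respondents are given their baseline scores.

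**The concern.** The test and the manual come from the same programme. At two months, possession of the manual follows allocation: one arm has been given it and the other has not. Participants answer an emailed link in their own time, so some of the trained arm could check answers in the manual. Randomisation does not balance this, because access is a consequence of allocation. The planned ANOVA sees only the score and cannot separate what a participant knew from what was looked up. Giving non-respondents their baseline score does nothing about look-up among those who respond.

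At stake is how the two-month knowledge result is read. If it is positive, a sceptical reader can attribute part of it to the book, and the article describes no data that would answer that. Information on the use of materials has to be collected with the test and cannot be recovered later.

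**Working it through.** **1. The plan's own figure.** 50 per group with 20% attrition gives 50 / 0.8 = 62.5, rounded up to 63, as Participants and sample size states. The present point does not alter this. The 50 and the correlation of 0.8 are used below.

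**2. How small a shift matters.** With 50 per arm, r = 0.8 and a two-sided 5% test (the article gives 5% without sidedness), the smallest significant difference in SD units is:

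- baseline-adjusted: 1.96 × √(1 − 0.8²) × √(2/50) = 1.96 × 0.6 × 0.2 = 0.24
- change score: 1.96 × √(2 × (1 − 0.8)) × √(2/50) = 1.96 × 0.632 × 0.2 = 0.25

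If the SD is 2 to 3 items, that is roughly 0.5 to 0.75 of an item out of 16.

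**3. Illustration of look-up.** The article gives no SD, look-up rate or gain, so these are assumptions. Let a share f of the trained arm look up and gain g items each, with no true effect, no look-up by controls and SD = 2.5 items.

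- Shift in the mean difference: f × g
- Standard error: √[(2 × 0.36 × SD² + f(1 − f)g²) / 50], where 0.36 = 1 − 0.8²
- Chance of a significant result favouring training: Φ(shift / SE − 1.96). With no look-up this is 2.5%.

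For f = 0.2 and g = 2, the shift is 0.4. The SE is √[(4.5 + 0.64) / 50] = √(5.14 / 50) = 0.321. Then 0.4 / 0.321 = 1.25, and Φ(1.25 − 1.96) = 0.24.

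| f | g (items) | Shift (items) | Shift (SD) | SE | Chance of false benefit |
|---|---|---|---|---|---|
| 0.1 | 1 | 0.1 | 0.04 | 0.303 | 5% |
| 0.1 | 2 | 0.2 | 0.08 | 0.312 | 9% |
| 0.2 | 2 | 0.4 | 0.16 | 0.321 | 24% |
| 0.2 | 4 | 0.8 | 0.32 | 0.376 | 57% |

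**4. Sensitivity to the assumptions.**

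- Model: a change-score variance (0.40 in place of 0.36) turns 9%, 24% and 57% into 9%, 22% and 54%.
- SD: for f = 0.2 and g = 2, the chance is 33% at SD 2 and 18% at SD 3.
- Control look-up: if a share h of controls also look up, from any source, with the same gain, the shift becomes (f − h) × g. With f = 0.2, h = 0.1 and g = 4 it falls from 0.8 to 0.4 items. With h = f it is zero, and with h > f it favours controls.

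**The case against.** **The manual is part of the intervention.** This stands. Stage 3 lists it among the course materials, so the randomised contrast is a valid effect of course plus manual. The article does not call the controlled two-month comparison one of retained knowledge; it speaks of maintained knowledge only for the 12-month follow-up of the intervention arm. What is limited is the reading of the score as unaided knowledge.

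**The questionnaire may already carry a closed-book instruction.** This also stands. The article is condensed and does not reproduce the questionnaire. A reader might infer that the test is open-book by plan, but silence does not show that. An instruction alone would leave access unequal, and would not show who complied.

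**The error need not favour training.** A reader might infer that it can run in only one direction. The article does not support that. Emailed controls can search other sources. At the first follow-up only they answer outside the classroom, which could work against the intervention. That wave enters the ANOVA too, so the net direction across waves is not established. At two months the known inequality is possession of the manual.

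**Materials open in the classroom.** A reader might also infer that the trained arm has its materials to hand at the first follow-up. Stage 4 says only that the questionnaire is completed there on a tablet. The point therefore rests on the two-month wave alone.

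**The magnitudes are all assumption.** Correct. The article does not say that the manual answers the 16 items, and a course that teaches the content leaves less to gain by look-up. Few may bother in a survey with nothing riding on the score.

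**Conclusion.** The concern holds as a limit on interpretation, confined to one component of the primary outcome at one wave. The mode of the two-month test and the timing of the manual are both fixed in the article, and together they tie access to the programme's own text to allocation. Within the range of assumptions shown, the consequence goes from negligible to a false significant benefit more often than not. The documents do not say where in that range the trial would fall. The point deserves action because the remedy is nearly free and must be in place before the data are collected.

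**What to change.** At all three waves and in both arms:

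1. Unless the questionnaire already has one, place an instruction directly above the 16 items to answer without consulting the manual, notes or the internet.
2. After the items, add one yes/no question on whether any material was consulted.
3. Report the answers by arm and wave.
4. Keep the main analysis on the scores as given. Pre-specify a supportive sensitivity analysis of the two-month knowledge score that leaves out admitted look-ups in both arms. Do not replace those scores by the baseline value under the rule for non-respondents, since that would credit trained participants who answered honestly with no gain. State that the analysis conditions on behaviour after randomisation, probably more frequent in one arm, and so is not a randomised comparison.

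The report should describe the two-month knowledge contrast as the effect of course plus manual.

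The cost is two lines in an existing online questionnaire and one extra analysis; sample size, intervention and schedule are unchanged. The limit is reliance on honest self-report: the bias is reduced and described, not removed.
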